**Data that is captured by the MedicineWise app**

The dataset for each patient in the intervention arm can be generated on a daily basis and exported in a spreadsheet format and can be used by the project team. The type of raw data that is captured is divided into four categories and described below. Further manipulations of this raw data may be necessary (e.g. to identify the participant and to calculate the number of doses missed) and will be carried out as part of the analysis in this study.

The 4 fields of data are:

1. **User ID** – the data extracted from the app will be a unique key that will then need to be de-identified to reveal the participant’s name, DOB, sex and email address. There will be a map provided at the beginning of the study once the participants have been recruited has downloaded and have registered with the MedicineWise app that will enable this process to occur, and a simple Excel matching function should make things easier
2. **Medicine details** – this will include all the medicines that the participant has on their medicines list in the MedicineWise app that are on the critical and non-critical list, and it would include the name of the medicine, strength and form.
3. **Dosage and frequency**– this will include how the patient has been instructed to take their medicines, as entered in the app. In addition to the dose and frequency, it will also include specific times that doses are due.
4. **Actual time when doses are recorded as taken**– when the doses are recorded as taken, timestamp of when that occurs is recorded by the MedicineWise app. The participant has the ability to change that time if they wish (e.g. if a medicine dose is due at 8am and took their dose at 8.30am but they only marked their dose as being taken at 6pm, the app will record the time taken as 6pm but the patient has the ability to change this back to 8.30am). The difference between the time taken and when the doses were supposed to be due will be calculated and used monitor medication adherence.

**Sample size**

Sample size calculations are focused on two different measures and were also done assuming equal numbers of participants in each group. The first measure takes into account an absolute increase in mean adherence of 15 % (Hulley et al., 2013). In this measure, at two tailed 0.05 significance level with a power of 80 % and standard deviation of 35 (Goldstein et al 2014), the number of participants required in each group is 86. In the second measure, the analysis is by comparing proportions of adherence (Hulley et al., 2013). Previous studies have estimated the adherence to cardiovascular drugs to be up to 60 % (Chowdhury et al., 2013; Bowry et al., 2010). In this measure, a total sample size of 182 participants is needed to provide 80 % power to detect an increase in the proportion of adherent participants from 60 % to 80 %, with a two tailed 0.05 significance level. Therefore, taking the larger of the two sample sizes (91 participants in each arm), and allowing for a 20 % loss to follow up, a total of 220 participants will be recruited in this study with each arm consisting of 110 participants.

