**Outcome measures**

Outcome measures will be collected at 3, 6 and 9 months following the baseline data collection at recruitment.

Primary outcome

The primary outcome is the comparison of medication adherence between the two arms. Medication adherence will be measured by self-reported medication adherence tool Self-Efficacy for Appropriate Medication Use Scale (SEAMS) (Risser et al., 2007). This has been validated previously in other cardiac conditions such as coronary heart disease (Risser et al., 2007). This self-reported data will also be verified by the data collected from the intervention arm participants whose adherence rate has been captured by the data collected by the NPS MedicineWise application.

Secondary outcomes

i. composite outcome of death or hospital admission related to HF or not related to HF. All instances of hospitalization and death will be recorded and classification as to whether it was HF related or not will be done by experienced cardiologists

ii. health resource utilization (ie. Primary and secondary care contacts, social care contacts and relevant medication use)

iii. health related quality of life, assessed by EQ-5D-5L

iv. self-reported medication adherence

v. assessment of exercise tolerance (6 min walk test)

vi. psychological wellbeing (Depression anxiety and stress scales)

vii. self-care of HF index questionnaire

viii. medication knowledge

ix. acceptability, utility and engagement with the NPS MedicineWise application (Satisfaction survey)

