**Data analysis**

The primary analyses will be based on a between-group (intervention arm vs control arm), intention-to-treat approach at the different time points. Continuous variables will be analysed using independent t-tests and discreet variables will be analyses using chi-squared tests. Where appropriate, other statistical tests will be employed depending on the nature of the data. Identification of any confounding baseline variables will be corrected by logistic regression analysis. All between group outcome results that are significant will be reported with odds ratios and 95 % confidence intervals. Statistical significance is set at α 0.05.

Qualitative outcomes

Thematic analysis will be carried out based on patient responses to open-ended questions in the functional assessments. This will enable to generate emerging and overarching themes. The analysis will characterise intervention arm participants’ observed and self-reported responses to the intervention and link these responses to the acceptability, utility and their engagement with the smartphone app. This thematic analysis will be based on the intervention arm participants’ responses collected at months 3 and 9, in addition to a satisfaction survey undertaken upon completion of the trial.

Economic outcomes

Data on the frequency and duration of hospital in-patient admissions will be obtained from medical records, and PBS and MBS utilisation data from Medicare following informed patient (or proxy in the case of moderate to severe cognitive impairment) consent. Unit costs will be derived from relevant hospital finance departments, published data sets including Pharmaceutical Benefits Scheme and Medicare Benefits Schedule and Australian Refined Diagnosis Related Groups (AR-DRG) cost weights.

A participant level analysis will be undertaken to determine the incremental costs and outcomes associated with the intervention relative to controls. Incremental cost effectiveness ratios and their associated confidence intervals will be estimated and cost effectiveness acceptability curves for varying threshold values of cost effectiveness will also be presented. An assessment of the sensitivity of the results obtained to variation in measured resource use, effectiveness and/or unit costs will be undertaken using appropriate one-way, multi-way and probabilistic sensitivity analysis.

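### One scored primary outcome is given two planned analyses, and a proportion 'adherent' with no stated cut-off sets enrolment; the full score at 9 months should be named as the single primary analysis

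*Protocol*

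**What the plan says.** Under Outcome measures, the primary outcome is a comparison of adherence between arms: "Medication adherence will be measured by self-reported medication adherence tool Self-Efficacy for Appropriate Medication Use Scale (SEAMS"). This is a scale. The Hypothesis section places the comparison at 9 months.

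The Sample size section gives two calculations for adherence:

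- A mean difference. "The first measure takes into account an absolute increase in mean adherence of 15" percent, "at two tailed 0.05 significance level with a power of 80 % and standard deviation of 35"; on these inputs "the number of participants required in each group is 86".
- A proportion. "In the second measure, the analysis is by comparing proportions of adherence". The target is "to detect an increase in the proportion of adherent participants from 60 % to 80 %, with a two tailed 0.05 significance level", which requires 182 in total at 80% power.

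The larger result, 91 per arm, is carried forward. With an allowance of 20% for loss to follow-up, it becomes 220 (110 per arm).

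The Data analysis section then states: "Continuous variables will be analysed using independent t-tests and discreet variables will be analyses using chi-squared tests". It does not say which test decides the primary hypothesis. It adds that confounding baseline variables will be handled by logistic regression and that significant between-group results will be given as odds ratios with 95% confidence intervals.

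**The concern.** The outcome is collected as a score, but the calculation that fixes the trial's size treats it as a yes/no status. The Protocol names no threshold on SEAMS and gives no reason for imposing one. Logistic regression and odds ratios belong to a binary outcome, so the analysis section points towards a dichotomy as readily as its t-test rule points towards the score. A team following this text could justify either test, and could pick the threshold late.

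Two things are at stake. The first is an open choice in the primary analysis. The second is power: cutting a score usually discards information, and here the full score is available at no extra cost. The two calculations may also rest on different effects. If so, the larger sample size is not a cautious version of the smaller one; it is an easier target tested with a less sensitive method.

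**Working it through.** **Inputs.** From Sample size: two-sided alpha 0.05, power 80%, difference 15, SD 35, proportions 0.60 and 0.80, loss 20%, 110 per arm. Evaluable per arm: 110 × 0.8 = 88. Assumed, not in the Protocol: one normal score with a common SD underlies both calculations, and the cut lies where 60% of controls are adherent.

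**1. The plan's own figures.**
- Means: n = 2(1.960 + 0.842)² × (35/15)² = 85.5, so 86 per arm. Reproduced.
- Proportions, mean proportion 0.70: n = [1.960√(2 × 0.70 × 0.30) + 0.842√(0.24 + 0.16)]² / 0.20² = 81.2, so 82 per arm. With continuity correction, (81.2/4) × [1 + √(1 + 4/(81.2 × 0.20))]² = 90.9, so 91 per arm and 182 in total. Reproduced.

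**2. Do the two effects agree under the assumed model?**
- Mean calculation: 15/35 = 0.43 SD.
- Proportion calculation: z(0.80) − z(0.60) = 0.842 − 0.253 = 0.588 SD, or 0.588 × 35 = 20.6 points.
- Adherent proportion implied by the 15-point shift: Φ(0.253 + 0.429) = 0.752.

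The second calculation therefore assumes the larger effect.

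**3. Power at 88 per arm.**
- Score, 15-point shift: Φ[0.4286 × √(88/2) − 1.960] = Φ(0.883) = 81.1%; noncentral t gives 80.7%.
- Proportion, 0.60 vs 0.752 (mean 0.676): null SE = √(2 × 0.676 × 0.324/88) = 0.0705; alternative SE = √((0.240 + 0.186)/88) = 0.0696. Power = Φ[(0.152 − 1.960 × 0.0705)/0.0696] = Φ(0.20) = 58.0%.

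| Effect | n per arm | Score (noncentral t) | Proportion (uncorrected) |
|---|---|---|---|
| 15 points, SD 35 | 88 | 80.7% | 58.0% |
| 15 points, SD 35 | 91 | 82.0% | 59.5% |
| 60% to 80% | 88 | 97.3% | 83.1% |

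Under the 15-point effect, the proportion test would need 147 per arm for 80% power (160 with continuity correction). At 88 per arm, a continuity-corrected test has about 52%.

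**4. How far does this depend on the assumed model?** All at 88 per arm with a 0.43 SD shift, against about 81% for the score:
- Normal score, cut where 30% to 80% of controls are adherent: 44% to 62%.
- Other symmetric shapes, 60% cut: uniform 41%, logistic 66%, t with 5 df 71%, Laplace 75%.
- Bounded (beta) score, SD 35% of the scale, 60% cut: 53% to 60% for control means of 48 to 60% of the scale, but 76% at a control mean of 65% and 96% at 70%.
- Same beta scores, cut at 80% of the scale: 73% to 98%.

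**The case against.** The strongest reply is that no binary primary analysis is fixed. SEAMS is a scale, and the Data analysis section assigns t-tests to continuous variables, so the natural reading is a t-test on the score. Sizing for both forms and taking the larger number leaves the score analysis above the 86 it needs. A cut-off is also the kind of detail a statistical analysis plan may supply. This stands in part: the Protocol does not commit to a dichotomy, and the absent cut-off alone would be no finding. It does not dispose of the point. The Protocol describes a proportion analysis of the primary outcome, lets it set enrolment, and prescribes binary-outcome methods for adjustment and reporting.

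A second reply is that the Sample size section presents two different measures, with different sources, and never says that 60% to 80% comes from cutting a variable with SD 35. This stands. The 75% and the 58% need a common distribution and a cut that the Protocol does not state. Normality is also doubtful for percentage-like inputs: with an illustrative control mean of 60 and SD 35, about 13% of controls would exceed 100.

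Third, the 15 and the 35 are expressed as percent adherence, and nothing shows that they are SEAMS units. This also stands and limits what the power statement can claim.

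**Conclusion.** The point holds as a defect in how the primary analysis is fixed. One scored outcome carries two planned analyses, the one that sets enrolment rests on an unstated cut, and the analysis section leaves both routes open. Under a common normal score the proportion test gives up about 23 points of power for the 15-point effect (80.7 − 58.0) and about 14 for the 60% to 80% effect (97.3 − 83.1). Those figures are conditional on shape and cut, and some skewed cases show no loss.

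Three stronger readings are tempting, and the document does not support them:

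- That the trial has only 58% power. That figure applies only if the primary test is the proportion and the assumed model holds. The score analysis keeps about 81% on the stated inputs.
- That the 80% power for 60% vs 80% is wrong. It reproduces at 91 per arm with continuity correction.
- That the two effects flatly contradict each other. They differ only if both describe the same roughly normal score.

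**What to change.** 1. In Sample size and Data analysis, state that the single primary analysis is the between-arm difference in the full SEAMS score at 9 months.
2. For that outcome, replace logistic regression and an odds ratio with baseline adjustment in a linear model and a mean difference with 95% confidence interval.
3. Make any proportion adherent a supportive summary that cannot decide the primary hypothesis, with its SEAMS cut fixed in advance.
4. Rest the primary power statement on the mean-difference calculation, after confirming that 15 and SD 35 apply to the SEAMS scale; if they do not, restate them in SEAMS units.
5. Keep the 60% vs 80% calculation only as supportive, noting that under normality it assumes a larger effect (about 0.59 SD against 0.43 SD). Do not write 58% into the Protocol, since it depends on an assumed distribution and cut.

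The cost is wording. The score is already collected, and 88 evaluable per arm meets the 86 required on the stated inputs, so no change in enrolment is needed. The small downside is that the headline result is a score difference and not a percentage adherent; the percentage can still be shown descriptively.

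### Recruiting 220 does not allow for the stated 20% loss: 182 evaluable participants need 228 enrolled, and 220 leaves 88 per arm against the 91 required

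*Protocol*

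**What the plan says.** The Sample size section of the protocol gives two calculations.

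- **Means:** "an absolute increase in mean adherence of 15" percentage points, with "standard deviation of 35 (Goldstein et al 2014), the number of participants required in each group is 86".
- **Proportions:** "a total sample size of 182 participants is needed to provide 80 % power" for a rise in the proportion adherent "from 60 % to 80 %, with a two tailed 0.05 significance level".

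It then chooses between them, "taking the larger of the two sample sizes (91 participants in each arm" in its own words, and fixes recruitment: "allowing for a 20 % loss to follow up, a total of 220 participants will be recruited in this study", which is 110 per arm. The Setting section repeats 220, and the random-number link under Randomisation and blinding is also set up for 220. The protocol gives no other loss rate and no rounding rule.

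**The concern.** An allowance for loss to follow-up should leave the required number after the loss has happened. The enrolled number is therefore the evaluable number divided by the proportion expected to remain. Here the enrolled number looks like the evaluable number increased by 20%, which is a smaller allowance than one for losing 20% of those enrolled.

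If so, four figures given together (80% power, 91 per arm, 20% loss, 220 recruited) cannot all be true. Anyone who recomputes the sample size will find that the trial misses its own target under its own assumption.

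**Working it through.** **Inputs, all from the Sample size section:** 60% versus 80%; two-sided 0.05 (z = 1.960); 80% power (z = 0.842); equal arms; difference in means 15 with SD 35; 20% loss; 220 recruited.

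**1. The two base figures reproduce.**

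Proportions, uncorrected, with average proportion 0.7:

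n = [1.960 × √(2 × 0.7 × 0.3) + 0.842 × √(0.6 × 0.4 + 0.8 × 0.2)]² / 0.20² = 81.2, so 82 per arm.

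With the continuity correction:

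n′ = (n/4) × [1 + √(1 + 4/(n × 0.20))]² = (81.2/4) × [1 + √1.246]² = 90.95, so 91 per arm and 182 in total.

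This matches the protocol, so its 91 is the continuity-corrected figure.

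Means: n = 2 × (1.960 + 0.842)² × 35²/15² = 85.5, so 86 per arm. This also matches.

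**2. The step from 182 to 220 does not reproduce.**

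| Step | Total | Per arm |
|---|---|---|
| Needed after loss | 182 | 91 |
| To enrol, dividing by 0.8 | 227.5, so 228 | 113.75, so 114 |
| Multiplying by 1.2 instead | 218.4 | 109.2, so 110 (220 in total) |
| Left from 220 after 20% loss | 176 | 88 |

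The shortfall is 6 participants, 3 per arm. The loss that 220 can absorb is 1 − 182/220 = 17.3%. The multiplication by 1.2 is inferred, since the protocol shows no inflation step, but taken per arm and rounded up it gives exactly 110.

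**3. Power at 88 per arm.**

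Proportions, continuity-corrected: z = [0.20 − 1/88 − 1.960 × √(0.42/88)] / √(0.40/88) = 0.79, so power is 78.5%. The same formula at 91 per arm gives 80.0%.

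Proportions, uncorrected: z = [0.20 − 1.960 × √(0.42/88)] / √(0.40/88) = 0.96, so power is 83.1%.

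Proportions, Fisher's exact test by enumeration: 78.9% at 88 per arm and 80.8% at 91.

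Means: z = 15/(35 × √(2/88)) − 1.960 = 0.88, so power is 81.1%.

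**The case against.** The strongest reply is that 220 falls short against only one of three reasonable targets. The primary outcome is a scale score (SEAMS), and the Data analysis section uses t-tests for continuous variables, so the means calculation is the closer match to the analysis. It needs 86 per arm; 86/0.8 = 107.5, so 108 per arm or 216 in total, and 220 covers that. The uncorrected chi-squared calculation needs 82 per arm; 82/0.8 = 102.5, so 103 per arm or 206 in total, and 220 covers that too. Even on the corrected basis the loss is 1.5 percentage points of power, which uncertainty in the rounded inputs could easily exceed.

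All of this stands as a statement about consequences, and it keeps the point modest. It does not rescue the sentence, because the protocol itself adopts the larger requirement and then claims that 220 secures it after 20% loss.

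It could also be argued that participants lost late would still contribute earlier data. The Study population section says data from those who withdraw will be left out of the final analysis, which would make each withdrawal a full loss. However, that rule covers withdrawal and not every kind of loss to follow-up, and it sits awkwardly with the intention-to-treat approach in the Data analysis section. The arithmetic here does not depend on it.

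**Conclusion.** The point holds. For 182 evaluable participants after a 20% loss, 228 must be enrolled. Enrolling 220 leaves 176.

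This takes the loss as 20% of those enrolled, which is the natural reading, and takes the protocol's own choice of 91 per arm as the requirement. On that basis power falls from 80.0% to 78.5%. On the other two bases it stays above 80%. This is an error in a stated planning figure with a small effect on the trial, and it is worth correcting because the correction is nearly free.

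**What to change.** Any one of these makes the Sample size section consistent:

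- **Keep 220 and 20%, and restate the power (preferred).** For example: with 220 recruited and 20% lost, 88 per arm remain, giving about 78% power for 60% versus 80% with continuity correction and about 83% without. This costs one sentence and a slightly less favourable stated figure, with no added participants.
- **Keep 220 and restate the tolerance.** Say that 220 preserves 91 per arm if loss does not exceed about 17%. This also costs one sentence. Word it as the loss the design can absorb, because the protocol offers no basis for 17% as an expected rate.
- **Recruit 228 (114 per arm).** This keeps 80% power on the adopted basis at the cost of 8 more participants. The Setting, Randomisation and blinding, and Sample size sections would all need the new number.

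Naming the continuity-corrected formula as the source of 91 would help readers reproduce it, but is optional.

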**Trial data collection**

Trial data will be collected at 4 time points (at baseline, 3, 6 and 9 months). Data will be collected at face-to-face during home visits, phone calls or via skype interviews (mainly for rural participants). To encourage participant retention and completeness of data, participants will receive a honourarium of AUD$30 in total at completion of the study.

At the point of recruitment into the trial, baseline data will be collected after written informed has been obtained by a member of the research team. The following information will be collected:

Sociodemographic information: Date of birth, gender, ethnicity, height, weight, education status, marital status, employment status, smoking status and health literacy

Medical history: comorbidities, NYHA class, standardised mini-mental state exam score, depression score, all prescribed and non-prescribed medication history

Laboratory test results: full blood counts, full electrolytes (sodium, potassium, urea, creatinine +/- magnesium), Hb, iron studies, NT pro BNP, liver function tests.

Functional assessment: QoL questionnaire using the Short Form 36 Health Survey version 2 (SF-36v2) (Ware JE; RAND Corporation 2015), Depression Anxiety and Stress Scales (DASS), Self-Care of Heart Failure Index (SCHFI) (Riegel et al., 2009), EQ-5D-5L questionnaire (Herdman et al., 2011) and drug adherence questionnaire, healthcare utilization (linkage data from Australian Pharmaceutical benefits Scheme and Medicare Benefits Schedule).

At the 3, 6 and 9 month follow ups, a member of the research team will record details of any changes to the participants’ medication or implantable cardiac devices, details of any hospitalisations or healthcare resource utilization since the last follow up. At each follow up interview, participants in the control arm will be asked whether they have used any drug administration aids or medication reminder app or other forms of electronic reminder systems for daily administration of medications. At the end of the study, intervention arm participants will complete a satisfaction survey to assess the acceptability, utility and engagement with the NPS MedicineWise application. Also, data about prescription refill rates and healthcare utilization will be gathered for all participants through data linkage with the Australian Pharmaceutical benefits Scheme and Medicare Benefits Schedule.

Data will be collected at each follow up on forms and then recorded as de-identified data only identified by the participant’s study number and stored electronically. At each follow up time point, 10 % of the data will be randomly selected for verification. In the event that discrepancies are identified, these will be verified using the original paper data sheet.

Participants’ names, addresses and smart phone numbers will be collected for the purpose of intervention delivery and participant interviews. All data collected from participants will otherwise be stored electronically as de-identified data which will be stored separately from identifiable data. All paper based data forms will be stored in locked filing cabinets within offices with restricted access. Electronic records will be stored in a secure server maintained by the University of South Australia. Data in the database will be backed up regularly. Access to all data will be restricted to the members of the research team and data will not be shared with any third parties.

